## Abstract

**Background:**

Out-of-hours (OOH) health care for acute medical problems is often challenged by long waiting time for callers in need of advice and triage. Allowing patients to bypass the OOH telephone waiting line may increase patient satisfaction and provide them with a feeling of safety. We aimed to develop an “emergency access button” enabling patients to bypass the normal telephone waiting line in out-of-hours primary care (OOH-PC) if they perceive their condition to be critical and to evaluate the effect of introducing the button in terms of patient satisfaction and their feeling of safety.

**Methods:**

All patients calling the OOH-PC in two different Danish health care regions during three months will be included in this randomized controlled trial. Data will be collected through two questionnaires developed for this study: a pop-up questionnaire on the relevance of bypassing the normal waiting line to be completed by triage professionals after patient contact and a paper/electronic questionnaire on perceived safety and satisfaction with the emergency access button to be completed by the callers. These questionnaires were developed and validated using external and internal expert feedback, focus group interviews and a two-week field test. The study will be conducted over three months with an estimated user-rate of the emergency access button of 3%.

**Discussion:**

We have developed an emergency access button and we now want to investigate whether this new option will influence upon the level of satisfaction and the feeling of safety in the calling patients. Additionally, the study will reveal the assessed relevance of the decision to bypass the line by triage professionals.

**Trial registration:**

Registered as NCT02572115 at Clinicaltrials.gov on October 5^th^ 2015.

## Background

Many countries offer several access options into the healthcare system for patients with acute health problems [1]. These include out-of-hours primary care (OOH-PC), emergency departments (ED) and emergency medical call centers such as the Emergency Medical Dispatch Center (EMDC-112) receiving emergency calls through the European emergency number 1-1-2. Although these entities target different healthcare needs, their patient population seems to be partly overlapping.

Out-of-hours care is an important part of primary healthcare; it is the point of entrance into the health care system for the many patients who contact health care outside normal working hours, i.e. between 4 p.m. and 8 a.m. on weekdays, in weekends and during holidays [2]. Out-of-hours care is thus intended to provide care for many different patient groups, and the services offered depend on the nature and the severity of the perceived health problem. The individual patient’s decision to contact a specific setting implies that the patient selects and chooses the point of access to out-of-hours care, and this choice also influences the care pathway [3]. An “inappropriate” choice may result in serious delay of treatment or insufficient intensive care, for example if primary care is contacted instead of the EMDC-112 in life-threatening situations [4]. However, overuse or overtreatment is a potential risk if patients call the EMDC-112 for minor problems [5, 6].

OOH-PC is provided by general practitioners (GPs) in large-scale organizations in four out of five Danish regions [2], whereas one region offers a medical helpline (MH-1813) serving as a publicly run call center. All persons calling OOH-PC or the MH-1813 must wait in line, even if the health problem is perceived as highly urgent or even life-threatening. As there is no option to bypass the telephone waiting line, the only alternative to waiting is calling the EMDC-112, which is intended for life-threatening situations that require immediate medical response, for instance dispatch of an ambulance. A previous study showed that approximately 1% of all OOH-PC telephone contacts are triaged directly to the EMDC-112. Additionally, approximately 5% of all patients estimate their condition as potentially life-threatening when calling OOH-PC [7]. One of the main reasons for calling OOH-PC is worry [8–10], and callers may experience distress due to long waiting time when calling with a perceived acute health problem [11]. A combination of long waiting time, worry and distress might lead to a low feeling of safety in callers.

Introducing an option to bypass the telephone waiting line could prompt a feeling of safety in callers and thus reduce the level of distress in medical situations. The Danish bypass option is inspired by a similar option in the Netherlands, but no research is currently available on the subject. The bypass option may increase the callers’ satisfaction with OOH-PC and the MH-1813 in general [12, 13]. It is important to ensure that such option is not misused as this might cause unnecessary long waiting time for the callers who choose not to bypass the line. Thus, we aim to develop and evaluate an emergency button that enables the caller to bypass the telephone waiting line in OOH-PC in the Central Denmark Region and in MH-1813 in the Capital Region of Denmark. We will study the frequency of emergency button use, the characteristics of the callers who choose to use the button compared with non-users and the effect of the bypass option on the callers’ reported feeling of safety and their level of satisfaction. Furthermore, we aim to investigate the triage professionals’ evaluation of the relevance of using the emergency button.

## Methods

### Design and setting

We will conduct a parallel randomized controlled superiority trial at the OOH-PC in the Central Denmark Region and in MH-1813 in the Capital Region of Denmark. These two settings were selected because they represent the two main organizational models for out-of-hours acute care in Denmark; they differ in access method, triage professional profile and waiting time (see Table 1). The comparison of data on emergency button use between these two regions provides us with documentation of the performance of the intervention and its generalizability. The study was developed in accordance with the SPIRIT guidelines [14].

**Table 1 Tab1:** Differences in out-of-hours telephone setup

Subject	OOH-PC in the Central Denmark Region	MH-1813 in the Capital Region of Denmark
Triage professionals	General practitioners^e^	Nurses and doctors^f^
Waiting time (90^th^ percentile, 2015)	7 min.^c^	16 min. 35 sec^d^
Waiting time (mean, 2015)	2 min. 30 sec^c^	6 min. 51 sec^d^
Waiting time (median, 2015)	1 min. 8 sec^c^	4 min. 29 sec^d^
Contacts per year (2014)	697,000^a^	911,000^b^
Inhabitants (per 1 Jan. 2015)	1,282,750^a^	1,760,000^a^
Contacts per inhabitant	0.54	0.52

Sources: ^a^Statistics Denmark, ^b^Capital Region of Denmark, ^c^Central Denmark Region, technical dep., ^d^Emergency Medical Services Copenhagen, Capital Region of Denmark, ^e^or doctors in final phase of GP specialist training, ^f^Can be GPs, doctors with other specialties than GP or doctors in training

In the Capital Region of Denmark, patients must call the MH-1813 if they need urgent medical advice; the telephone is primarily answered by triage nurses. They have the option to give telephone advice, forward the call to a doctor (most often with other specialties than general practice), triage to a consultation at an ED, refer to hospitalization, plan a home visit or dispatch an ambulance or forward the call to the EMDC-112. In the Central Region of Denmark, OOH-PC is run by GPs; all telephone calls are answered and triaged by GPs. They can offer a telephone consultation, triage to a clinic consultation or a home visit, refer directly to an ED/hospitalization or forward the call to the EMDC-112. Both the GPs in OOH-PC and the nurses/doctors in MH-1813 are referred to as *triage professionals*.

### Participants

All callers contacting the OOH-PC in the Central Denmark Region and the MH-1813 in the Capital Region of Denmark in the study period are invited to participate. A welcome message on the telephone will inform about the study and give the caller the opportunity to decline participation by pressing “1”. We will not include patients who have died since the index call or patients in the age group 14–17 years because of confidentiality issues (they sometimes contact OOH-PC without the knowledge of their parents). Callers can be included only once, even if they have several contacts during the study period.

### Intervention

Callers are routinely asked to type in the unique civil registration number (CRN) of the patient whom the call concerns on their telephone when calling OOH-PC and MH-1813; approximately 90% of all callers provide this information. The callers will be allocated into two arms according to their date of birth (even versus uneven date of the month), which is part of the CRN. This will ensure that a patient will be randomized to the same arm if s/he calls multiple times during the study period. The included patients will receive only one questionnaire regarding their first contact. One arm will be the control group, whereas the other arm will be the intervention group (see Fig. 1).

**Fig. 1 Fig1:**
[figure not shown]
Flowchart of intervention

For those in the intervention arm, the message on the answering machine will inform callers of the option to bypass the waiting line by pressing “9”. If the caller chooses to press “9”, the call will be answered by the next available triage professional. The triage professional will not know whether the caller has used the emergency button or not when answering the call. Callers in the control arm will get the usual message on the answering machine without the option to bypass the line. If the caller does not type in the CRN, s/he will not be included in the study and will be redirected to receive the usual message on the answering machine.

### Data collection

Data for this study will be collected by two types of questionnaires and information from the electronic patient record system.

### Triage professional questionnaire

A questionnaire will pop up on the work station of the triage personnel for each emergency button user immediately after termination of the contact. For every pop-up questionnaire concerning an emergency button user, a similar questionnaire will pop up for a random group of non-users in the intervention arm and for a random group of callers in the control arm (see Fig. 1).

The pop-up questionnaire contains seven items and can be completed in less than one minute. Three validated items origin from a GP pop-up questionnaire used in an earlier study on OOH-PC contacts [15]. These questions focused on reason for encounter, level of urgency and probable diagnosis. Four additional items were developed specifically for the new pop-up questionnaire; two measuring the relevance of the caller’s choice to bypass the line as seen from a strictly medical point of view and a psychosocial point of view and two focusing on the caller and the reason for encounter. The face validity was assessed with the help from seven GPs with solid OOH-PC experience. The GPs provided feedback on the formulation of questions and on the feasibility of answering the questionnaire when being on duty. The content validity was assessed through ten internal feedback rounds within the author group and with the research department’s communication specialist. The questionnaire was field-tested during two weeks of January 2016 (see Table 2).

**Table 2 Tab2:** Experiences from the field test

Call statistics	Triage professional questionnaire	Caller questionnaire
3% bypassed the line	Easy to complete	43% response rate
38% declined participation	Approx. 70% GP participation from start of shift	Focus groups: - Items easy to understand - Rephrase three items - Support of the intervention
10% did not type in civil registration number		

### Caller questionnaire

Questionnaires will be sent to all callers for whom the triage professional has completed a pop-up questionnaire. The questionnaire is intended to be answered by the caller, who will also be the patient in most cases. As the questionnaire is posted to the patient for whom the CRN was entered, it will not always be possible to get the caller to answer the questionnaire, for example if the caller was not the patient or a relative in which case the patient will be asked to complete the questionnaire. The caller questionnaire contains 23 questions and differs for the three groups on only one topic, depending on the use of the emergency button (see Table 3). The developed questionnaire consists of a mix of validated items from former studies [7], items from existing validated scales, i.e. SF-36 [16] and GAD-2 [17], and newly developed items. Content validity was assessed through ten internal feedback rounds within the author group and with the research department’s communication specialist. Face validity was assessed through a field test, which was conducted during two weeks of January 2016, and through two semi-structured focus group interviews, which were performed in May 2016; these interviews focused on the definition and understanding of safety from a caller perspective and served to further clarify and specify the wording of the items (see Table 3).

**Table 3 Tab3:** Participant groups and questionnaire content

Groups	Triage professional questionnaire	Caller questionnaire
All three groups: common content of questionnaire	Reason for encounter - Symptom - Possible diagnosis Severity of condition New illness/injury or exacerbation of chronic illness/injury	Background information: - Gender, age, civil status, educational level, ethnicity - Mental and physical health Questions regarding the specific contact: - Reason for encounter - Severity of condition - Caller’s expectations - Satisfaction with the specific contact General questions: - General feeling of safety with the service - General satisfaction with different health services
	Additional questions	Additional questions
Intervention group: “users” Get the option to bypass the line	Questions regarding the evaluation of the relevance of bypassing seen from a medical perspective Questions regarding the evaluation of the relevance of bypassing seen from a psychosocial perspective	Questions regarding the emergency access button: - Feeling of safety - Recommendation of implementation
Intervention group: “non-users” Get the option to bypass the line, but choose not to	Question regarding whether the caller should have bypassed the line or not	Questions regarding the emergency access button: - Feeling of safety - Recommendation of implementation
Control group	Question about whether the caller should have bypassed the line or not	

The caller questionnaire will be sent a few days after the contact to reduce the risk of recall bias. We plan to use the digital mailbox linked with the unique Danish CRN (this mailbox is currently being tested for reliability and response rate) and surface mail for patients without a digital mailbox (approximately 10%). The digital mailbox approach will allow us to email a unique link for an internet questionnaire, which is easily accessible for callers. If the patient is less than 14 years old, the questionnaire will be addressed to the parents. For electronic questionnaires, a reminder will be sent one week and two weeks after the contact. For paper questionnaires, one reminder will be sent three weeks after the contact (for cost reduction).

### Electronic patient record system

We collect information for all contacts in the study period from the electronic patient record systems of both OOH-PC and the MH-1813: CRN of the patient, date and time of contact, triage outcome (i.e. telephone consultation, clinic consultation, home visit, referral to ED or referral to hospitalization), use of emergency button and estimated waiting time in the telephone line at the time of the call. If the caller has chosen to bypass the line, we will also collect information about the length of the waiting time at the time of the bypass.

## Outcome measures

### Primary outcome measures

Frequency of bypassing among callersCaller satisfaction and feeling of safety; button users versus non-usersRelevance of button usage assessed by triage professional

### Secondary outcome measures

Characteristics of button users versus non-users (e.g. age, gender and reason for encounter)Reasons for using/not using the emergency access button

## Study period and power calculations

We performed power calculations to assess the number of respondents needed to answer our main research question on feeling of safety and to assess the expected duration of the study period to ensure valid estimates of emergency button use. As both the number of button users and the response rate of caller questionnaires can influence the length of the study period, we performed two power calculations: one based on response rate and another based on number of button users.

### Response rate

Our main outcome measures on satisfaction and feeling of safety will both be measured by a 5-point Likert scale. We want to be able to detect a mean difference of at least 0.3 between button users and non-users. If we assume that the sample standard deviation is 1, the significance level is 5%, the power is 95% and given a mean of 3, we need a total of 290 completed patient questionnaires for each of the three groups to be able to detect a difference of 0.3 between two groups.

Our field test showed that approximately 40% of all callers chose not to participate in the study, and 10% did not type in their CRN, thus leaving them out of the randomization (Fig. 2). In 2014, approximately 700,000 contacts were made to the OOH-PC in the Central Denmark Region [18]. This gives us a study population of 50% out of 700,000, i.e. 350,000 for one year. Of these, 50% would be randomized into the intervention arm (175,000); 3% of these would use the emergency button (5,250). The field test also showed that approximately 70% of the triage personnel chose to participate in the study (3,675) and that the response rate of the caller questionnaire was approximately 40% (1,470). Thus, we will get 123 answered questionnaires from button users per month if the above-mentioned conditions are taken into account. To collect 290 questionnaires per group, the duration of the study period must be approximately 2.4 months.

**Fig. 2 Fig2:**
[figure not shown]
Flowchart of power calculation

### Number of button users

To investigate the frequency of bypassing the line, we need to determine the user rate. Our field test in the OOH-PC service in the Central Denmark Region showed a user rate of approximately 3% for the emergency button, which gives 5,250 users in one year (see Fig. 2). To ensure satisfactory power in our calculations regarding choice of the bypass option, we aim for a 95% confidence interval (CI) of +/− 0.8% (2.2%; 3.8%). This means that we need at least 1,950 button users, which will require a study period of 2.7 months.

On the basis of the calculations from the field test of the OOH-PC services in the Central Denmark Region, we expect that a period of no more than three months will be required to complete the study. As more contacts per year are directed to the MH-1813 in the Capital Region of Denmark (approximately 910,000) and the response rate of the MH-1813 triage professionals is also expected to be higher due to an obligation by the management to participate in the study, the study period is expected to run for less than three months. The study is planned to take place at the same period of time in the two selected settings.

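### The requirement of 1,950 button users in 2.7 months follows neither from the stated precision, which needs about 1,750 to 1,880 callers offered the button, nor from the stated accrual, on which 1,950 users take about 4.5 months

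*Protocol article*

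**What the plan says.** The section Number of button users, under Study period and power calculations, starts from the field test in the Central Denmark Region, which "showed a user rate of approximately 3% for the emergency button, which gives 5,250 users in one year". It sets the target precision as a 95% interval from 2.2% to 3.8% and then concludes: "This means that we need at least 1,950 button users, which will require a study period of 2.7 months". From the Central Denmark figures it infers that "we expect that a period of no more than three months will be required to complete the study".

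The accrual rate comes from the preceding section, Response rate: "This gives us a study population of 50% out of 700,000, i.e. 350,000 for one year". Half of these contacts (175,000) go to the intervention arm, and 3% of that half gives the 5,250 users. That section also derives a duration of about 2.4 months from a target of 290 completed questionnaires per group.

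**The concern.** Two things do not fit. First, a confidence interval for a user rate is governed by its denominator, here the intervention-arm callers who hear the offer. A requirement stated in users is in the wrong unit, and 1,950 is far too large as a number of users for a half-width of 0.8 points. Second, 1,950 users in 2.7 months cannot be reconciled with 5,250 users in twelve months, a figure given in the same paragraph.

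The sentence is the only size justification given for the frequency of bypassing, and it supplies the longer of the two durations quoted before the three-month limit. As it stands, a reader cannot tell whether the trial has reached its stated size for this outcome: in Central Denmark the literal user target is missed at three months, while the stated precision is met within days.

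**Working it through.** **Inputs, all from the protocol article.** User rate p = 0.03 and half-width d = 0.008 at 95% (Number of button users). 175,000 intervention-arm contacts and 5,250 users a year (Response rate), that is 175,000/12 = 14,583 contacts and 5,250/12 = 437.5 users a month. About 910,000 contacts a year in the Capital Region (Number of button users).

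**1. Trying to reproduce 1,950 from the precision target.** n = z² p(1 − p)/d² = 1.96² × 0.03 × 0.97/0.008² = 1,747 callers, containing 0.03 × 1,747 = 52 users. Other intervals, judged by half-width:

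| Interval | Callers | Users at 3% |
|---|---|---|
| Wald | 1,747 | 52 |
| Wilson | 1,772 | 53 |
| Agresti-Coull | 1,800 | 54 |
| Wald, continuity-corrected | 1,870 | 56 |
| Clopper-Pearson | 1,877 | 56 |

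Requiring instead that the upper limit not exceed 3.8% gives 2,195 to 2,218 callers with the Wilson, Clopper-Pearson and Agresti-Coull intervals. None of these returns 1,950, and none comes near 1,950 users.

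**2. What 1,950 would deliver under each label.**
- As callers: 1.96 × √(0.03 × 0.97/1,950) = 0.0076, or 0.76 points, which rounds to the stated 0.8.
- As users: 1,950/0.03 = 65,000 callers, with half-width 1.96 × √(0.03 × 0.97/65,000) = 0.0013, or 0.13 points, about six times tighter than stated.

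A number of callers labelled as users is therefore a plausible origin, but the text does not say so.

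**3. Trying to reproduce 2.7 months.** 1,950/437.5 = 4.46 months. In 2.7 months 2.7 × 437.5 = 1,181 users accrue, and in three months 3 × 437.5 = 1,312.

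**4. Time to the stated precision.** 1,747/14,583 = 0.12 months and 1,877/14,583 = 0.13 months, about four days either way. Three months in Central Denmark give 3 × 14,583 = 43,750, with half-width 1.96 × √(0.03 × 0.97/43,750) = 0.0016, or 0.16 points, five times tighter than the target.

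**5. The whole trial.** Applying the Central Denmark rates to both regions (an assumption): (700,000 + 910,000) × 0.5 × 0.5 × 0.03/12 = 1,006 users a month. That is about 3,019 in three months, and 1,950 in 1.9 months.

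**6. The questionnaire calculation.** 5,250 × 0.7 × 0.4 = 1,470 a year, or 122.5 a month, and 290/122.5 = 2.4 months. The standard two-mean formula (difference 0.3, SD 1, power 95%, two-sided 5%) gives 289 per group against the stated 290. This part reproduces.

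**The case against.** **The trial runs in two regions.** A reader might infer from 1,312 against 1,950 that the trial misses its own size by a third. The documents do not support that: 1,312 is a Central Denmark figure, and both regions together would pass 1,950 in about two months. What stands is the contradiction inside the paragraph, because the paragraph bases its duration on Central Denmark and uses that region's 5,250.

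**The three-month period does not need this figure.** This is also right. The 2.4 months from the questionnaires supports a limit of three months on its own, so the error does not show the study period to be too short.

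**Some combination of factors might produce 2.7 months.** Pooling the regions and applying the 70% triage participation gives 1,006 × 0.7 = 704 users a month and 2.8 months. Using the field test's 52% participation as well gives 1,610,000 × 0.52 × 0.5 × 0.03 × 0.7/12 = 733 a month and 2.7 months. The text describes neither route. It presents the Capital Region as a reason for a shorter period, not as part of the 2.7 months. Nor is triage participation needed to count button presses, which come from the electronic patient record system. Neither route would repair the 1,950. The power flowchart (Fig. 2) is not available here, so the origin of both numbers stays unknown.

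**Repeat callers.** The Participants section says: "Callers can be included only once, even if they have several contacts during the study period". The 2.4 months counts contacts, so it is slightly optimistic. A reader might go further and argue that heavy repeat calling pushes it past three months, but the documents give no information on how calls cluster within patients. Under purely random calling (an assumption) at 0.54 contacts per inhabitant a year (Table 1), about 94% of contacts in three months are first contacts, and 2.37/0.935 = 2.5 months. Against this, the calculation rounds the field test's 38% refusal up to 40% and its 43% response down to 40%.

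**Conclusion.** The sentence is wrong on both counts. The stated precision needs about 1,750 intervention-arm callers (Wald) and up to about 1,880 by half-width with an exact interval, that is 52 to 56 users. The printed 1,950 users is about 37 times the Wald figure (1,950/52.4). On the paragraph's own accrual, 1,950 users take about 4.5 months, not 2.7. The second result is a single division. The first rests only on the stated 3% and 0.8 points, and the choice of interval does not change the conclusion. The yearly figures are contacts, not distinct callers. Counting each caller once would lengthen the 4.5 months, and the precision target would still be met early in the study.

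The error lies in the stated requirement and its duration. It does not show a shortfall for the trial as a whole or an inadequate study period. Once corrected, the precision target no longer limits duration; the questionnaires from button users do.

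**What to change.** Reword the paragraph in Number of button users:

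- State the requirement in callers: a 95% half-width of 0.8 points at a 3% user rate needs about 1,750 to 1,880 intervention-arm callers, depending on the interval (about 52 to 56 button users), expected within about the first week in Central Denmark. Name the interval.
- Remove the 1,950 users and the 2.7 months, or correct them with a derivation. If 1,950 was meant as callers, say so; if it serves another analysis, state which one and give a duration consistent with 437.5 users a month or with an explicitly pooled rate.
- Give the expected half-width over three months, about 0.16 points in Central Denmark.
- State that duration rests on the 290 questionnaires from button users (2.4 months as calculated), and note that this counts contacts although each caller enters once, so it is slightly optimistic.

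The cost is one reworded paragraph. Enrolment, study period and questionnaire target are unchanged.
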